## Abstract

**Introduction:**

Around 40% of adults have pre-hypertension (blood pressure between 120–139/80–89), meaning they are at increased risk of developing hypertension and other cardiovascular disease-related conditions. There are limited studies on the management of pre-hypertension; however, guidance recommends that it should be focused on lifestyle modification rather than on medication. Self-monitoring of blood pressure could allow people to monitor and manage their risk status and may allow individuals to modify lifestyle factors. The purpose of this study is to determine the feasibility and acceptability, to both healthcare professionals and people with pre-hypertension, of blood pressure self-monitoring.

**Methods and analysis:**

A prospective, non-randomised feasibility study, with a mixed-methods approach will be employed. Eligible participants (n=114) will be recruited from general practices, pharmacies and community providers across Lancashire and South Cumbria. Participants will self-monitor their blood pressure at home for 6 months and will complete questionnaires at three timepoints (baseline, 6 and 12 months). Healthcare professionals and participants involved in the study will be invited to take part in follow-up interviews and a focus group. The primary outcomes include the willingness to engage with the concept of pre-hypertension, the acceptability of self-monitoring, and the study processes. Secondary outcomes will inform the design of a potential future trial. A cost-analysis and cost-benefit analysis will be conducted.

**Ethics and dissemination:**

Ethics approval has been obtained from London–Fulham NHS Research Ethics Committee, the University of Central Lancashire Health Ethics Review Panel and the HRA. The results of the study will be disseminated via peer-reviewed publications, feedback to service users and healthcare professionals, and to professional bodies in primary care and pharmacy.

**Trial registration number:**

ISRCTN13649483.

STRENGTHS AND LIMITATIONS OF THIS STUDYRecruiting in North West England, which has some of the highest levels of deprivation and worst cardiovascular disease health outcomes in the UK.Utilises services from across primary care (general practice, pharmacy and community providers), with the aim of reaching people with pre-hypertension who are likely to be of working age and who might not attend general practice.Questionnaire includes clinically validated tools.Twelve-month follow-up to allow exploration of longer term outcomes.Requirement for individuals to attend a face-to-face appointment for blood pressure eligibility check for those identified through GP electronic records.

## Introduction

People with blood pressure (BP) in the pre-hypertension (PHT) range (120–139/80–89 mm Hg^1^) have an increased risk, compared with those with normal BP, of developing hypertension^2^ and cardiovascular disease (CVD)-related conditions.^3–10^ It is estimated that 40% of adults have BP in the PHT range and this is increasing.^11^

PHT itself is not regarded as a disease, rather it is a warning of progression of BP to problematic levels requiring intervention.^12^ PHT can be a useful sign to alert those at-risk of developing hypertension and CVD, so they can take action to delay or reduce their risk of progression to disease status.^12^ Guidance recommends that PHT management should be focused on lifestyle modification rather than relying on medication as in hypertension.^13^ Prospective cohort studies have shown that by making lifestyle changes, people with PHT can significantly reduce both their risk of developing hypertension^14^ and also reverse PHT to normotensive levels.^15 16^

Evidence from other conditions such as hypertension^17^ and diabetes^18^ shows that self-monitoring (SM) approaches are effective in reducing CVD risk by supporting lifestyle changes. However, unintended negative consequences (UNCs) of such interventions have been reported including anxiety,^19^ poorer self-rated health^20^ and social stigma.^21^ There are also concerns that intervening at the ‘pre-risk’ stage has the effect of labelling, as well as medicalising, the normal.^22^ However, other evidence suggests that making people aware of PHT does not lead to negative effects and may be beneficial.^23 24^

While the technology and procedures involved in SM of BP are already well established in hypertension management, it is premature to assume it will be a feasible, acceptable or effective option for PHT, as the recommended management pathway for the two differ. While a trial to test the effectiveness of SM for PHT is needed, there is currently a scarcity of data to inform its design.^23 24^

The primary aim of REVERSE is to determine the feasibility and acceptability, to both individuals and health care professionals (HCPs), of SM of BP for people with PHT. The results will determine the appropriateness, and design of any future multi-centre, randomised trial to investigate whether SM helps in detecting and increasing awareness of PHT, as well as encouraging lifestyle changes to reduce risk of hypertension and associated CVD.

## Methods and analysis

### Design

The REVERSE study is a prospective, non-randomised feasibility study, using mixed-methods. The study began in October 2021 and will be completed by the end of March 2024.

### Setting

General practices, pharmacies and a community health check provider from across Lancashire and South Cumbria, selected based on Index of Multiple Deprivation (IMD) category (low, mid and high) to ensure socio-economic variation and geographical spread, will act as participant identification sites (PICs).

A search of electronic patient records will be the primary method of identification in general practice. Of those identified as potentially eligible, batches of 50–100 will be randomly chosen and posted a letter of invitation and participant information sheet.

Pharmacies and the community health check provider will identify potential participants when they complete NHS health checks or BP checks. General practice can also opt into this route.

Individuals with a BP reading in the PHT range (second reading 120–139 mm Hg systolic and/or 80–89 mm Hg diastolic) will be offered a participant information sheet and given their health/BP check results summary, including their BP readings, height and weight.

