### Participant recruitment

Recruitment for the main study will take place between June 2022 and January 2023. Individuals who have received an information sheet and are interested in taking part will be asked to contact the research team.

As last recorded BP in general practice may have been measured some years previously (especially due to COVID-19), interested individuals will be required to have a BP check, usually completed with the research team, to confirm that their BP is currently in the PHT range.

Individuals identified via a health/BP check in a pharmacy, the community or general practice will have their eligibility confirmed on the initial phone call with a member of the research team, before having an on-line baseline research appointment.

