#### Eligibility criteria

Inclusion criteria: aged 18 years and over; BP in the PHT range (120–139/80–89 mmHg).

Exclusion criteria: current or previous diagnosis of hypertension; prescribed anti-hypertension medication; pregnant; life-limiting illness; history of stroke, heart attack or other significant CVD; being unable to understand verbal and written English.

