#### SM of BP for 6 months

After their training, each participant will start SM at the beginning of the following month. Participants will be asked to SM their BP for 3 consecutive days, starting on the first Monday of each month, for 6 months. The time of day that readings are taken can be decided by the participant but to minimise confounding factors, the time must be kept consistent throughout the 6 months of SM, ensuring they are done no sooner than 30 min after food or exercise and that the timing of medications in relation to readings is kept the same.

Participants will be asked to record two BP readings, along with the time each reading was taken, on each measurement day. They will colour code the second reading on each day as follows:

Green for BPs in the normal range (systolic BP (SBP) <115 AND diastolic BP (DBP) <75 mm Hg),Amber for those in the PHT range (SBP 115–134 OR DBP 75–84 mm Hg),Red for those in the hypertensive range (SBP≥135 OR DBP ≥85 mmHg).

These ranges are based on standard clinical guidelines^1^ but have been reduced by 5/5 mm Hg as recommended for home BP readings. Modified ranges will be provided to relevant participants, for example, the range for those with diabetes will be 10/10 mm Hg lower than guidelines.

After each month’s three measurement days, participants will colour code the overall month as follows:

If there have been any Red days, the month should be classed as Red,If there were no Red days and more Amber than Green days, the month should be Amber,If there were no Red days and more Green than Amber days, the month should be classed as Green.

Red, Amber and Green correspond to hypertensive, PHT and normotensive, respectively. If participants' readings are categorised as hypertensive (Red), over 2 consecutive months, they will send their readings to their GP using a covering letter provided by the research team.

Participants will email, post or telephone their readings, colour coding and actions to the research team each month.

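### The pre-hypertension blood pressure rule leaves the second component unbounded and is worded differently in two sections, so readings the protocol itself classes as hypertensive can satisfy it

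*Protocol article*

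**What the plan says.** Five places in the protocol article bear on who counts as pre-hypertensive.

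- **Setting.** People whose check gives a "second reading 120–139 mm Hg systolic and/or 80–89 mm Hg diastolic" are offered an information sheet.
- **Eligibility criteria, inclusion.** Entry requires "BP in the PHT range (120–139/80–89 mmHg". The text does not say whether one component or both must lie in range.
- **Eligibility criteria, exclusion.** Hypertension is excluded through "current or previous diagnosis of hypertension; prescribed anti-hypertension medication". No exclusion refers to a measured value.
- **Participant recruitment and Baseline research appointment.** People found through general practice records have a new blood pressure check "to confirm that their BP is currently in the PHT range". Those found at a health or blood pressure check "will have their eligibility confirmed on the initial phone call with a member of the research team", and no repeat measurement is described for them. Eligibility is checked again before consent. None of these steps restates the range.
- **SM of BP for 6 months.** The home scheme has three colour bands, including "Red for those in the hypertensive range (SBP≥135 OR DBP ≥85 mmHg". The home ranges are the guideline ranges, which "have been reduced by 5/5 mm Hg as recommended for home BP readings".

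**The concern.** A rule joined by *and/or* is met as soon as one component is in range, whatever the other is. The home scheme works the other way: one component at or above its cut-off makes the reading hypertensive. The same level of blood pressure can therefore be pre-hypertensive at identification and hypertensive on the scale used afterwards.

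The study is meant to describe self-monitoring in people with pre-hypertension, and the Introduction justifies it partly because pre-hypertension and hypertension are managed differently. People with undiagnosed hypertensive-range readings would plausibly have more Red months, more letters to the GP, more consultations and referrals, and perhaps more health anxiety. Those are the feasibility, resource-use and unintended-consequence summaries that a future trial would draw on. The proportion found eligible, a secondary outcome, also depends on which reading of the criterion a site or researcher applies.

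**Working it through.** **Step 1. Reproduce the home bands.** Inputs: clinic range 120–139/80–89 (Eligibility criteria) and the 5/5 mm Hg reduction (SM of BP for 6 months).

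- Systolic: 120 − 5 = 115 and 139 − 5 = 134.
- Diastolic: 80 − 5 = 75 and 89 − 5 = 84.

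These match the stated Amber band of 115–134 and 75–84.

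**Step 2. Recover the clinic hypertensive cut-offs.** Red starts at 135/85. Adding back the offset gives 135 + 5 = 140 systolic and 85 + 5 = 90 diastolic, either component sufficient. No outside guideline is needed.

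**Step 3. Apply each reading of the rule to test values.**

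- Setting rule: systolic 120–139 OR diastolic 80–89.
- Inclusion criterion read as both: systolic 120–139 AND diastolic 80–89.
- Capped rule: the Setting rule AND systolic <140 AND diastolic <90.

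| Reading | Hypertensive (Step 2) | Setting rule | Inclusion read as both | Capped rule |
|---|---|---|---|---|
| 150/85 | yes | accept | reject | reject |
| 130/95 | yes | accept | reject | reject |
| 150/75 | yes | reject | reject | reject |
| 150/95 | yes | reject | reject | reject |
| 130/85 | no | accept | accept | accept |
| 130/75 | no | accept | reject | accept |
| 115/85 | no | accept | reject | accept |

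Two things follow. The Setting rule accepts 150/85 but rejects 150/75, so a higher diastolic value brings a person in; that is hard to see as intended. And neither reading of the inclusion criterion resolves matters: as either component it equals the Setting rule and keeps the gap, while as both components it closes the gap but rejects 130/75 and 115/85, which Setting accepts.

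**Step 4. Look for the limit elsewhere.** The exclusions depend on diagnosis or medication. The records-route check, the phone confirmation and the pre-consent check all refer back to the range without defining it. The home Amber band has the same open OR: home readings of 145/80 and 125/90 meet both Amber and Red, and precedence is stated only for the month, not for the day.

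**Step 5. Size.** The article gives no blood pressure distribution, so a count cannot be derived. As illustration only, assume bivariate-normal screening values with means 120–132/74–80, SDs 14–17/9–11 and correlation 0.4–0.7. In five simulated scenarios within those ranges, 12% to 30% of people meeting the Setting rule had systolic ≥140 or diastolic ≥90 (11.9% to 30.4% before rounding). Applied to the target of 114, that is 0.119 × 114 ≈ 14 to 0.304 × 114 ≈ 35. The calculation does not remove diagnosed or treated people and ignores every later check, so under these assumptions it is an upper bound, not a forecast.

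**The case against.** The strongest reply has four parts.

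1. *The Setting rule governs invitation, not entry.* This stands. The rule decides who is offered an information sheet; the inclusion criterion decides entry. A reader might infer that the *and/or* rule by itself enrols hypertensive people, and the document does not support that. The gap reaches enrolment only if the inclusion criterion is read as either component. If it is read as both, the gap closes, but the two sections then disagree.

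2. *The intent is clear from the three-category scheme.* This largely stands. Normal, pre-hypertensive and hypertensive are set out as separate categories, and the same open OR in the Amber line suggests drafting shorthand in which the higher category prevails. So this is a wording defect, not a decision to include hypertensive readings. Several kinds of provider and two confirmation routes must still apply the criterion, and its written form should not need interpreting.

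3. *Later checks would catch it.* This stands in part. It would be too strong to say that nothing later can catch such a person. Invitees in the health-check route hold their own readings, so a phone caller could ask for them, and eligibility is checked before consent. But these checks use the same undefined range.

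4. *An article condenses the full protocol, and the analysis is descriptive.* The fuller document may carry a clean rule. The point here is not a missing detail, however: the article states an operational rule, and that rule misclassifies. It is true that no hypothesis test depends on it and that a subgroup analysis by baseline blood pressure is planned. That lowers the severity. The subgroup analysis would not by itself identify out-of-range entrants, because its categories are still to be decided.

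**Conclusion.** The point holds as a moderate wording defect. As written, the Setting rule accepts readings such as 150/85 and 130/95 that the protocol's own scheme classes as hypertensive, and the inclusion criterion either shares that gap or contradicts Setting. This rests only on the article's stated ranges, its either-component definition of Red and its 5/5 mm Hg offset.

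How many participants are affected is unknown. A reader might take the simulated 14 to 35 of 114 as an expected number of hypertensive participants. The document does not support that, because the distribution is assumed, diagnosed and treated people are left in, and the later checks are ignored. The true number could be small or nil if staff applied the probable intent.

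**What to change.** Reconcile Setting, Participant recruitment, Eligibility criteria and the colour-band definitions in SM of BP for 6 months, and have the authors confirm the intended population. If it is the one the three-category scheme implies, a single definition built from the protocol's own categories would do: at least one component in the pre-hypertension range and neither in the hypertensive range. On the clinic scale this is the capped rule in the working. It rejects 150/85 and 130/95 and keeps 130/85, 130/75 and 115/85.

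Use that wording for the invitation, the records-route check, the phone confirmation and the pre-consent check. In the phone route, record the actual qualifying reading. State also how a home day that meets both Amber and Red is to be coded.

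Flag any enrolled participant whose qualifying reading falls outside the definition. Report the main feasibility, resource-use and unintended-consequence summaries with and without them.

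The cost is a sentence in each affected section and in the site instructions, a slightly smaller eligible pool, and one extra descriptive sensitivity analysis.

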### Participant recruitment

Recruitment for the main study will take place between June 2022 and January 2023. Individuals who have received an information sheet and are interested in taking part will be asked to contact the research team.

As last recorded BP in general practice may have been measured some years previously (especially due to COVID-19), interested individuals will be required to have a BP check, usually completed with the research team, to confirm that their BP is currently in the PHT range.

Individuals identified via a health/BP check in a pharmacy, the community or general practice will have their eligibility confirmed on the initial phone call with a member of the research team, before having an on-line baseline research appointment.

#### Eligibility criteria

Inclusion criteria: aged 18 years and over; BP in the PHT range (120–139/80–89 mmHg).

Exclusion criteria: current or previous diagnosis of hypertension; prescribed anti-hypertension medication; pregnant; life-limiting illness; history of stroke, heart attack or other significant CVD; being unable to understand verbal and written English.

#### Sample size

We aim to recruit and train 114 individuals on the study procedures. Based on an estimated attrition rate of 20%, this will result in 90 participants remaining in the study at the 6-month follow-up.

### Data collection

Data associated with the primary and secondary outcomes listed below, participant demographic and clinical information, and monthly self-monitored BP readings will be collected. The patient-reported data will be collected at baseline, 6 months and 12 months. Additionally, anonymised data will be provided from the PICs to enable description of the overall population that the sample came from.

### Primary outcomes

The primary outcome for this study is to determine whether SM for PHT is feasible and acceptable to both individuals with PHT and to HCPs. This will be assessed by exploring;

#### Willingness to engage with the PHT concept and the SM intervention

Assessed using the number and proportion of services and individuals approached expressing an interest in taking part at the time of recruitment.

#### Acceptability of the intervention and study processes

Explored during service provider and participant interviews and questionnaires, covering: (a) opinions and experiences of the study processes and the intervention; (b) barriers and facilitators to SM; (c) suggested changes and improvements; (d) ease of integration into current practice.

### Secondary outcomes

#### Recruitment rates of participants and service providers

Assessed from the proportion of PICs enrolled and actively identifying potential participants, the time taken to recruit the target sample and the proportion of people who are eligible and who consent to take part.

#### Attrition rates and completeness of data

Measured throughout the recruitment period: proportion of people who attend each study timepoint, number withdrawing definitively and from just the intervention, reasons for withdrawal, proportion of missing data.

#### Protocol adherence

Measured throughout the study, including the number, frequency and timing of self-monitored readings; correct action taken each month; accuracy of recorded readings; reasons for non-adherence.

#### Fidelity to the SM

Measured at 6-month follow-up, competency assessments for research team delivering participant training; number of participants deemed as competent to self-monitor during baseline sessions; proportion of appropriate home readings entered into GP clinical systems after 6-month follow-up.

#### Incidence and impact of any UNCs, healthcare resource use and quality of life

Measured at baseline, 6 months and 12 months, health anxiety assessed using the Health Anxiety Inventory (HAI) short version^25^; depression assessed using the Patient Health Questionnaire (PHQ-9)^26^; healthcare utilisation using a participant questionnaire which will capture the consultations, medications and referrals attributable to the intervention, and quality of life assessed using the EQ-5D-5L.^27^

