#### Economic analysis

A cost analysis and a cost-benefit analysis will be undertaken. The cost analysis will quantify the health resource utilisation associated with SM. The resource use information will be determined using:

Self-reported data at baseline, 6 and 12 months on the participants’ health resource utilisation (eg, medications, consultations and referrals due to their PHT) and will be instrumental in estimating any change pre-study and post-study.Data on human resources (eg, training time) employed to set up the SM obtained from the research team at baseline.

Costs will be quantified by multiplying the resource use expressed in natural units by the unit costs drawn from published sources.^34 35^ SM set-up costs will be calculated in the same way. Where standard costs are not available, costs from published works or expert opinion will be used. The cost-benefit analysis will be based on a WTP using an established approach.^28^

Participants will complete a questionnaire at 6 months that captures key factors relevant to buying a BP machine, the maximum price they would be willing to pay and why. The distribution of the WTP values and how they compare against retail prices for similar BP machines will be determined. Regression analyses will identify potential associations between demographic and clinical variables and the WTP values. As part of the WTP analysis, information about the participants’ health-related quality of life will be collected using the EQ-5D-5L^27^ at baseline, 6 months and 12 months to measure change and estimate Quality Adjusted Life Years (QALYs) from baseline to 6 months and from 6 to 12 months.

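### Healthcare use is defined in two ways, and the definition tied to the intervention cannot support the planned pre-study to post-study change

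*Protocol article*

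**What the plan says.** Two sections of the Protocol article describe the resource-use data.

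- **Secondary outcomes (unintended negative consequences, healthcare resource use and quality of life).** One sentence covers all the measures under this heading, and its opening sets the timing: "Measured at baseline, 6 months and 12 months, health anxiety assessed using the Health Anxiety Inventory (HAI) short version". Healthcare utilisation comes later in the same sentence, through a participant questionnaire "which will capture the consultations, medications and referrals attributable to the intervention".
- **Economic analysis.** The cost analysis uses "Self-reported data at baseline, 6 and 12 months on the participants’ health resource utilisation". An example follows in brackets, introduced by *eg*: "medications, consultations and referrals due to their PHT". The stated purpose is that these data "will be instrumental in estimating any change pre-study and post-study".

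Two further sections fix the order of events. Under Baseline research appointment, the participant completes the questionnaire first; only then is a training date set and the monitor supplied. Under SM of BP for 6 months, "After their training, each participant will start SM at the beginning of the following month".

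**The concern.** A before-and-after comparison needs a quantity that can be observed on both sides of the start of the intervention. Use caused by the intervention cannot exist before it starts. If the questionnaire follows the outcome section, baseline carries no information, and what is called a change is simply the follow-up count.

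All participants self-monitor, so there is no control group, and pre-study versus post-study is the only contrast the cost analysis has. Self-monitoring might replace some practice or pharmacy blood pressure checks. A count that starts at zero cannot show that, and a planner of the future trial could take the result as a net added cost. The count also rests on each participant's own view of why a contact took place.

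**Working it through.** The plan gives no figure for healthcare use, so there is none to reproduce. The sample size (114 recruited, 90 expected at 6 months) does not enter the argument. The check is on the definitions, with assumed numbers as illustration.

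**Notation, per participant and over equal periods**

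- B: relevant use before the study, whatever its cause.
- F: relevant use at follow-up, whatever its cause.
- A: the part of F that the participant attributes to the intervention, with 0 ≤ A ≤ F.
- U = F − A: follow-up use not so attributed.

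**Step 1: outcome-section definition.** The baseline questionnaire precedes training and self-monitoring, so attributable use at baseline is 0. Recorded change = A − 0 = A ≥ 0.

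**Step 2: a definition that applies at both times.** Change = F − B, which can take either sign.

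**Step 3: the difference between the two.** A − (F − B) = A − (A + U − B) = B − U. The recorded change departs from the actual change by exactly the amount by which other use fell. If other use is unchanged (U = B), the two agree. If self-monitoring displaces existing contacts (U < B), the recorded change is too high.

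**Step 4: illustration.** All contact rates are assumptions; none comes from the documents.

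| B | F | A | U = F − A | Actual change F − B | Recorded change A | Difference B − U |
|---|---|---|---|---|---|---|
| 0 | 0.5 | 0.5 | 0 | +0.5 | +0.5 | 0 |
| 0.5 | 0.5 | 0.2 | 0.3 | 0 | +0.2 | 0.2 |
| 0.5 | 0.3 | 0.1 | 0.2 | −0.2 | +0.1 | 0.3 |
| 1.0 | 0.6 | 0 | 0.6 | −0.4 | 0 | 0.4 |

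In the third row the sign is wrong. In the fourth a real fall is recorded as no change. In the first the definition does no harm.

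**Step 5: economic-section definition.** Use related to pre-hypertension can occur before the study. Setting describes participants identified at NHS health checks or blood pressure checks, and Participant recruitment refers to earlier readings in general practice, some of them possibly years old. B may therefore be low, but it is not fixed at zero, and F − B can be negative. Only blood-pressure-lowering medication is zero at entry, because people prescribed it are excluded.

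**Side by side.** The time points are the same and so, evidently, are the data, but the scopes differ. Only the economic scope is compatible with the stated analysis.

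**The case against.** The strongest reply is that the article condenses a fuller protocol and the questionnaire is not shown. The phrase in the outcome section is one clause under a heading about unintended consequences, where use caused by the intervention is a natural interest. The baseline form may ask something broader. The cost analysis is planned in the economic section, so its wording could be taken to govern. Resource use is a secondary outcome of a feasibility study, and the cost-benefit analysis rests on willingness to pay, not on this difference. All of this stands and limits severity and confidence. It does not remove the conflict: the article states a scope, time points and a use for the data, and under the outcome-section scope these do not fit together.

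A second reply is that an all-cause count in an uncontrolled study also picks up unrelated illness and changes over time, so restricting to condition-related use is legitimate. That is fair. All-cause use is one acceptable basis, not the only one.

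A reader might infer three stronger claims that the documents do not support:

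- **That baseline is also zero under the economic wording.** The *eg* marks the pre-hypertension items as an example, and pre-study checks could count. The Introduction's remark that "PHT itself is not regarded as a disease" does not show that nobody consults about it.
- **That the change can only be an increase.** Zero change is possible even under the narrow definition, and use can fall between 6 and 12 months.
- **That the cost analysis is biased in a fixed direction.** Step 3 shows the error is B − U, which is zero if other use is stable and negative if it rises.

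**Conclusion.** The point holds as an inconsistency with a definite consequence. Under the outcome-section definition, baseline use is zero for every participant, so change from baseline cannot be negative and cannot reveal a saving or substitution. Under the economic-section definition it can. The two sections need to be reconciled before a pre-study to post-study change is reported.

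The size of any error in the cost result cannot be calculated from the documents; in the assumed cases above it runs from 0 to 0.4 contacts per person. The conclusion assumes that the questionnaire follows the outcome-section wording and that both sections describe the same data. Severity: should be fixed. Confidence: moderate, because the instrument cannot be inspected.

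**What to change.** Use one definition in the outcome and economic sections, and make it one that applies before and after the intervention: either all healthcare use or all blood-pressure-related use, over the same look-back period at baseline, 6 and 12 months. Record attribution to self-monitoring as a separate item. Base the pre-study to post-study change on the common count and show attributed use as a breakdown.

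If only intervention-attributable use has been collected, report it as use during follow-up and do not present it as a change from baseline.

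The cost is rewording one questionnaire section, slightly more recall burden for participants and a noisier count, most of all if all use is chosen. If the questionnaire already asks the broader question, only the outcome-section wording needs correcting.
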